### Adverse events

Adverse events are not collected specifically but noted when observed and reported to the research team for discussion. Since parent-driven interventions are non-pharmacological, safe and have no known side effects we are not expecting any adverse events.

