Pain alleviating pharmacological agents such as oral sweet solutions, i.e. sucrose and glucose, are today part of standard care in neonatal and postnatal care and are considered to have a calming and analgesic effect on infants during painful procedures [32]. Sweet solutions have been extensively investigated and found to reduce procedural pain from blood-sampling procedures in preterm, term infants and infants ≤12 months old, without serious side effects [33]. However, there is a consensus that non-pharmacological strategies should be the first choice in procedural pain management for infants because there are no adverse effects and parents can be involved using these approaches safely [23, 34, 35]. Non-pharmacological pain management involves interventions driven by nurses and/or parents. Just like oral sweet solutions, swaddling, containment or facilitated tucking, positioning, non-nutritive sucking and recorded music stimulation, are nurse-initiated pain alleviating interventions where parents can be included but parental presence is not required [32, 36]. Among the non-pharmacological approaches, the biopsychosocial perspective strongly supports parent-driven interventions [37]. In the parent-driven non-pharmacological interventions, the parent herself/himself is a mediator for pain relief [36]. Parent-driven non-pharmacological interventions are consistent with modern family-centered care in which the best interests of the infant and family are put ahead of staff convenience [36]. SSC, breastfeeding and live singing are simple and cost-effective evidence-based interventions that may modify the infant’s pain and stress if the strategies are well-timed [38–41]. SSC is a method widely used in postnatal care globally. A significant amount of research has also shown the pain-relieving effect of skin-to-skin contact during painful procedures in newborn infants [19, 42]. Breastfeeding has demonstrated efficacy that is equal to, or greater than, sweet taste interventions in reducing behavioral and physiological responses to pain in full-term infants undergoing venipuncture with no demonstrated adverse outcomes [38]. Live parental infant-directed lullaby singing, informed by music therapy research, has not been previously investigated during painful procedures. It has been confirmed in previous research in non-painful contexts that live parental lullaby singing is an individually tailored, non-verbal, multisensory, affective, relationship-based tool useful in regulating the infant, augmenting the parent’s focus on the infant in the moment, enhancing the parent’s emotional availability and responsiveness and decreasing stress in the dyad [43–45]. Previous research with recorded music stimulation with instrumental lullaby music, selected in consultation with an accredited music therapist, has shown similar effect to the current gold standard of oral sucrose [46], and the combination of music stimulation with sucrose provides better pain relief during blood sampling than when sucrose or music is used alone [46]. Recorded mother’s voice has also shown similar pain alleviating effects as oral sweet solutions [47, 48].

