**Fig. 1 Fig1:**
[figure not shown]
Timeline for the SWEpap study

Blinding will not be possible for the nurse and parents during the procedures. Since only the infant’s face and pulse oximetry will be videotaped, the subsequent PIPP-R pain assessment and GSR measurements will be blinded using muted recordings. The parents’ participation in the study is voluntary and they are informed in advance that they can withdraw at any time without giving any reason.

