## Methods: data collection, data analyses and management, data monitoring

### Data collection

Demographic data of the parent-infant dyad is registered before the procedure starts, including registration of potential music and singing activities during pregnancy for the parents in group 3. In all groups: before, during and after the procedure the infant will have a saturation probe attached to one foot making it possible to measure heart rate and oxygen saturation and electrodes measuring galvanic skin response on the other foot. The infant’s face and pulse oximetry values will be videotaped for later pain assessment with PIPP-R. An experienced midwife/nurse will perform the venipuncture. Venipuncture is routinely used in all hospitals in Swedish neonatal and postnatal care since it is considered less painful for the infant than heel lance [56]. A tourniquet using a soft cotton band is applied, the skin is disinfected, and a 21–23 Gauge needle is used for the blood sampling. The infant will be monitored until the treatment is concluded. In case of failed attempts, only the first venipuncture will be used in the study. In the breastfeeding condition, the midwife/nurse will make sure that the infant is latched and sucking well before the blood test is performed to safeguard the analgesic effect of breastfeeding. The infants’ behavioral responses to pain together with oxygen saturation and heart rate values are videotaped with two digital video cameras and will be assessed subsequently from the video films.

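### Adverse events are noted passively by people who know the allocation, so a report of no events would have unknown ascertainment and could not support the safety statements or a comparison between arms

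*Protocol article*

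**What the plan says.** The Adverse events section of the protocol article reads: "Adverse events are not collected specifically but noted when observed". Anything noted goes to the research team to be discussed. The reason follows at once and is given for the parent-driven interventions only: they are non-pharmacological, "safe and have no known side effects we are not expecting any adverse events". Ethics and dissemination repeats that these interventions are safe.

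Four other places bear on the rule:

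- **Blinding** (Recruitment and allocation, text after Fig. 1): "Blinding will not be possible for the nurse and parents during the procedures". Only the later scoring is masked: "the subsequent PIPP-R pain assessment and GSR measurements will be blinded using muted recordings".
- **Monitoring** (Data collection): "In all groups: before, during and after the procedure the infant will have a saturation probe attached to one foot". The infant's face and the oximeter values are filmed, and the stated use of the film is PIPP-R scoring.
- **Glucose** (Background): group 1 receives oral glucose, which the article lists under "Pain alleviating pharmacological agents such as oral sweet solutions, i.e. sucrose and glucose". The same section reports that sweet solutions have been widely studied without serious side effects.
- **Outcomes**: no safety outcome is listed.

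**The concern.** This is a stated rule, not a detail that a condensed article leaves to a fuller document. An analysis plan cannot recover events that were never written down.

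The rule has three weaknesses:

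- Nothing defines an event, and no entry is required for an infant in whom nothing was noticed. A blank record may mean no event or no one looking.
- The nurse and the parents, who are best placed to notice an event, know the allocation. The researcher who opens the envelope and guides the parents knows it too. The protocol also tells its staff that no events are expected. The setting differs by arm: examination table in group 1, parent's chest in groups 2 and 3.
- The reason given does not extend to group 1. The article's basis for regarding glucose as safe appears only in the Background, and the Adverse events section does not draw on it.

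What is at stake is the meaning of the safety sentence in the final report. The authors assert safety in two sections, and in the Discussion they hope that the results will inform care of critically ill infants. Readers may take a line saying that no adverse events occurred as evidence from this trial.

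**Working it through.** The protocol states no figure for adverse events, so there is none to reproduce. The calculations below show scale only.

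**Inputs.** From Sample size: 75 infants enrolled per group, 63 needed. Detection probabilities and event rates are assumptions, because the documents give none.

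**1. What zero events would mean with complete ascertainment.** The exact one-sided 95% upper bound for 0 of n is 1 − 0.05^(1/n).

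- n = 75: 1 − 0.05^(1/75) = 3.9%
- n = 63: 1 − 0.05^(1/63) = 4.6%

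The upper limit of the two-sided 95% interval for 0 of 75 is 1 − 0.025^(1/75) = 4.8%.

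**2. What zero noted events would mean under passive noting.** If the true rate is p and a fraction d of events is noticed, the rate of noted events is p × d. Zero noted in 75 bounds p × d at 3.916%, so the bound on p is 3.916% / d.

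| Assumed detection d | Upper bound on true rate |
|---|---|
| 1.00 | 3.9% |
| 0.50 | 3.916 / 0.50 = 7.8% |
| 0.25 | 3.916 / 0.25 = 15.7% |

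Nothing in the plan allows d to be estimated.

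**3. What unequal noticing would do to a comparison.** With the same true rate in two arms, the ratio of noted rates is d1 / d2. Assumed detection of 90% and 50% gives 0.9 / 0.5 = 1.8; 80% and 40% gives 2.0. At a true rate of 5% and detection of 90% and 50%, the expected noted counts are 75 × 0.05 × 0.9 = 3.4 and 75 × 0.05 × 0.5 = 1.9.

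**4. What complete collection could show.** The formula is the two-sided 5% test of two proportions with pooled variance under the null: power = Φ{(|p1 − p2|√n − 1.96√(2p̄(1 − p̄))) / √(p1(1 − p1) + p2(1 − p2))}, with n = 75.

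- 5% v 20%: Φ{(0.15 × 8.660 − 1.96 × 0.4677) / 0.4555} = Φ(0.84) = 0.80
- 5% v 10%: Φ{(0.05 × 8.660 − 1.96 × 0.3725) / 0.3708} = Φ(−0.80) = 0.21

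The normal approximation is rough at such small counts, but the message is clear. Even perfect collection detects only large differences.

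**5. Who would be in the denominator.** Recruitment and allocation excludes infants whose parent does not adhere to the allocated treatment, while Data analyses promises intention-to-treat with all randomised dyads. If the exclusion were applied, an event that interrupted the allocated treatment could disappear with the infant's record. An event list must therefore cover every randomised infant.

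**The case against.** The other side has substantial points.

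- **Infants are not unwatched.** They are monitored until treatment ends, with an experienced midwife or nurse and the same equipment in every arm. PIPP-R already scores heart-rate and saturation changes in each infant. A reader might infer that events are caught only by luck; the documents do not support that. What is missing is a definition and a uniform record.
- **Glucose is not an unaddressed risk.** A reader might infer one from the silence of the Adverse events section. The Background reports no serious side effects for sweet solutions, so the gap is in the stated reason for the rule.
- **Safety is not a trial objective.** The infants are healthy and the procedure is one brief routine test. The safety statements are prior assumptions, not planned conclusions. This limits the weight of the point, but it does not make a passive count interpretable once reported.
- **Unequal noticing is possible but not shown.** No passage demonstrates it, and the detection rates above are assumed.
- **The films are not a ready-made, fully blinded safety record.** The length of the recording is not stated. PIPP-R needs only a 15 s baseline and the first 30 s of the procedure, whereas skin-to-skin contact and singing start 10 minutes earlier. Film of the face may reveal breastfeeding to the scorer, and events off camera would still rest on unblinded observers.

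These points narrow the claim and shape the fix. They do not answer the central one: under the rule as written, an absence of noted events has unknown completeness.

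**Conclusion.** The point holds as a modest improvement to make before enrolment. As written, the adverse-event record has no known ascertainment, so it can support neither the safety statements in Adverse events and in Ethics and dissemination nor a valid comparison between arms. With complete ascertainment, 0 of 75 would exclude rates above about 3.9%. The 7.8% and 15.7% bounds rest on assumed detection of one half and one quarter and show only how quickly that statement weakens.

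A reader might go further and infer that the pain results are compromised. They are not: neither the primary nor any secondary outcome depends on the event record, and PIPP-R and GSR assessment is planned as blinded. Nor would the fix turn the trial into a safety comparison, since power at 75 per arm is only 0.21 for 5% against 10%.

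**What to change.** Before the first infant is enrolled:

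1. Fix a short event list, with definitions set by the investigators. Complete it for every randomised infant in all three arms, including those whose parents do not adhere to the allocation, with an explicit entry where nothing occurred.
2. Read saturation and heart-rate events from the videotaped oximeter values over one window that the recordings cover in all arms. Ideally score from the oximeter display alone, so that breastfeeding is not visible.
3. Record events that the film cannot show on a uniform bedside form, and state that this part is unblinded.
4. Report counts by allocated group with exact confidence intervals, as descriptive only.
5. Extend the rationale in the Adverse events section to group 1, or point to the Background for it.

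The cost is one short form per infant and some added scoring time, without new staff or procedures. The investigators should first confirm how long the recordings run, because that sets the common window.

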### Ethics and dissemination

The study is approved by the Swedish Ethical Review Authority (Dnr 2020–01562) and registered at ClinicalTrials. Gov (NCT04341194) in April 2020. Parents will receive both written and verbal information about the study. Written informed consent will be acquired from both parents of each participant. The Swedish Patient Injury Insurance is valid. The parent-driven interventions are non-pharmacological, safe and have no known side effects. The study complies with the ethical conduct of neonatal pain trials [57] by providing pain management for all involved infants and avoiding separation of the newborn infant and her/his parent. The results from the SWEpap-study will be published in scientific journals, in a doctoral thesis and presented at scientific conferences. In order to make our research more accessible to the public, the results will also be presented at health care related workshops and seminars, published in popular science journals and family and parenting magazines and communicated with the media (newspapers, radio, television and social media).

## Discussion

This study protocol describes a randomized controlled trial where the pain reliving effects of combined parent-driven pain management during venipuncture on newborn infants will be studied. Parents are a valuable resource in procedural pain management in newborn infants, a resource which has not been addressed in research until the last decade. In the SWEpap study, we emphasize the importance of parent involvement in newborn pain management, but the key question is to address the research gap in the literature of the efficacy of combined non-pharmacological parent-driven pain management. Combined parental soothing behaviors that provide rhythmic (holding/rocking/vocalizing) or orogustatory/orotactile (feeding/pacifying) stimulation that keep the parent close to the infant, are effective in a painful context [58]. Consequently, in the SWEpap study, we include parental live lullaby singing, which is an unexplored but promising biopsychosocial, multimodal and multisensory pain alleviating adjuvant, especially in combination with SSC and breastfeeding [37]. Newborn infants are highly responsive to social and affective communication. In live parental infant-directed singing, the parent is attuned to the moment-to-moment psychological experience of the infant [43, 59]. The mainly “physical” parent-driven interventions with SSC and breastfeeding are therefore accompanied by a relationship-based intervention, the live parental lullaby singing, which may assist in modifying the painful situation for both the infant and the parent before, during and after the painful procedure [37].

In research, SSC is most often provided by mothers [60]. There are few studies exploring gender differences, mothers versus fathers, or pain alleviating differences in SSC between the mother and her partner or a non-related woman. When testing paternal versus maternal SSC to reduce pain from heel lance, mothers were marginally more effective than fathers in decreasing pain response [61]. Non-related women who provide SSC for procedural pain in preterm neonates are marginally less effective than mothers at decreasing pain response [60, 62].

Within the interdisciplinary research field of neonatal pain, there is a small number of research studies that have addressed the parents’ voice and musical presence during painful procedures [63, 64]. However, the nature of the parents’ vocal and musical engagement with their infants was not systematically reported. The parental live singing was not described and differentiated from “babytalk”, reciting of nursery rhymes or reading a story [64]. In general, live infant-directed singing is considerably more effective than infant-directed speech in lowering infants’ elevated arousal levels and ameliorating distress [65]. Analyses of parents’ singing to their infant in a non-painful context, have revealed similarities in the singing style of mothers and fathers, for example fathers, like mothers, adjust their singing with slower tempo and with warmer vocal tone when singing to infants than in other contexts [66, 67]. The soothing, comforting and emotion regulating properties of a lullaby are well-known cross-culturally and historically [65]. To date, research about parental infant-directed singing has focused primarily on the importance of the mother’s voice, but the possibility for fathers and partners to partake in live lullaby singing with their infant may facilitate a more equal parenthood [68, 69].

In the SWEpap study, multiple methods will be used when assessing the infants’ pain; GSR which comprises neurophysiological signs of pain and stress, and PIPP-R which is a widely used and validated pain assessment instrument. In addition, according to the parent-driven practice where parents are integrated in procedural support, the parents in the SWEpap study will also be assessing their infant’s pain. Pain assessment is as subjective as the pain experience itself and it is important to recognize the reciprocal relationship between infant and parent in a pain assessment context [39]. Parents are acknowledged as having a crucial role in assessing the infant’s pain and taking appropriate action to manage it [70]. Research has also shown that the parent’s assessment is not always based on the infant’s behavior [71] and may therefore differ from the health care professionals’ assessment [72].

To reduce the risk for selection bias in this study, broad inclusion criteria will be used including also parent-infant dyads from other cultures who understands English or Swedish, which strengthens the results and generalizability. A strength in this study is that data collection will take place in four hospitals in diverse health care regions in Sweden which will hopefully increase the scientific quality by recruiting a large sample size within a feasible time period, increasing the generalizability to other settings and reduce the risk of recruitment bias. The allocation with group 2a and b, referring to two different groups receiving skin-to-skin contact, might be considered as problematic. However, performing clinical research sometimes makes it difficult to use standardized procedures. It is not ethically feasible to defer from already existing guidelines and, in this study, preventing mothers from breastfeeding if applicable. It is important to focus on relevant clinical situations where the results can be useful for the patients, families and various health care settings and not only conducting research in laboratory surroundings. An aspect that must be taken into consideration is how to empower parents to use their voice and sing in conjunction with painful procedures. Parents might feel shy and inhibited about singing, especially in unfamiliar situations among unfamiliar people. On the other hand, research shows that most parents (60%) already sing spontaneously to their newborn during hospitalization [73]. By starting the lullaby singing together with SSC 10 min before the venipuncture and giving the parents clear instructions how the singing should be performed, we might modulate possible concerns. The use of technical equipment during the venipuncture will add a few minutes to the procedure, however the research group has previous extensive experience of similar research projects that will ensure the implementation of the study protocol.

The results generated in the SWEpap study will hopefully contribute to the interdisciplinary endeavor world-wide of involving and integrating parents in neonatal pain management and presumably also inform pain management practice in the neonatal intensive care context, where the critically ill and vulnerable hospitalized infants suffer the most from repeated, cumulative and inadequately treated procedural pain in addition to separation from the parents.

## Data Availability

The datasets used and/or analyzed during the current study are available from the corresponding author on reasonable request.

## Abbreviations

FCC: Family-centered care
GSR: Galvanic skin response
NICU: Neonatal intensive care unit
PIPP-R: Premature infant pain profile-revised
RCT: Randomized controlled trial
SSC: Skin to skin contact
PIDS: Live parental infant-directed lullaby singing
VAS: Visual analogue scale
